Evaluate the effects of cardiorespiratory exercise and Chinese herbal medicine, both individually and in a combination, on rehabilitation on pulmonary function among patients with COVID-19 through four intervention groups, including a cardiorespiratory exercise plus Chinese herbal medicines group, a cardiorespiratory exercise group in isolation, a Chinese herbal medicines group, and a waiting list control group (primary outcome). We hypothesize that the combination of cardiorespiratory exercise and Chinese herbal medicines will more greatly facilitate the rehabilitation of patients with COVID-19.Reveal whether and how the gut microbiome plays a role in the effects of cardiorespiratory exercise and Chinese herbal medicines, both individually and in combination, on the rehabilitation of impaired pulmonary function. We hypothesize that the combination of cardiorespiratory exercise and Chinese herbal medicines will better modulate the gut microbiome and the related metabolites and thus better mediate the effects.Assess the effects of cardiorespiratory exercise and Chinese herbal medicines on immune functions, both individually and in combination, on the rehabilitation of other relevant symptoms and signs of COVID-19. We hypothesize that the combination of cardiorespiratory exercise and Chinese herbal medicines will better modulate the immune function and thus better mediate the effects.Evaluate the effects of cardiorespiratory exercise and Chinese herbal medicines, both individually and in combination, on recovery from mental health-related outcomes (loneliness, stress, anxiety, depression) and on quality of life (QoL). We hypothesize that the combination of cardiorespiratory exercise and Chinese herbal medicines will better help postdischarge patients in recovery from mental health-related outcomes and improve their QoL.Assess the lasting effects of cardiorespiratory exercise and Chinese herbal medicines after a 12-week follow-up period. We hypothesize that some effects (eg, dyspnea, mental health-related outcomes, QoL) will be sustainable, while others (outcomes sensitively responded to cardiorespiratory exercise, eg, physical fitness, lung function) will partially relapse after the intervention cessation.

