### Sample Size Calculation

Aiming to achieve a large effect size of 0.8, based on a meta-analysis of effectiveness of exercise interventions on dyspnea and exercise capacity in patients with pulmonary fibrosis diseases [28], using a significance level of 0.05, power level of 90%, and 20% drop-out rate, a sample size of 172 patients (43 per group) was preliminarily estimated for the study. The meta-analysis result was chosen because there is no similar rehabilitation program available that combines exercise and Chinese herbal medicine. Furthermore, the outcome variables in that meta-analysis are similar to our primary outcomes. Given that the effects of Chinese herbal medicine were not considered, the final sample size will be re-estimated using preliminary outcomes from the pilot study.

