### Statistical Analysis

A generalized linear mixed model will be used to compare between-group differences in changes of outcome variables at the 12- and 24-week periods of the study, where group and time are the two factors of interest. Mediating effects of the gut microbiome and immune function tests will be determined by fitting linear regression models for pulmonary and other outcomes, respectively. A significance level of 0.05 will be adopted (two-tailed test). Intention-to-treat procedures will be applied to the data sets obtained. Missing data will be imputed using multiple imputations with chained equations, except for those from dropouts, which will be imputed with the baseline data. Data will be scrutinized for normal distribution prior to data analysis. Sensitive analyses, such as per-protocol analysis, as-treated analysis, and analysis for complete cases, will only be performed to assess the robustness of the data analyses.

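### Giving every dropout the baseline value in the main analysis shrinks a real effect, can create a false one if dropout differs by arm, and adds artificial relapse at week 25

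*Protocol article*

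**What the plan says.** All of the following is in the Protocol article.

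- **Statistical Analysis, missing data:** "Missing data will be imputed using multiple imputations with chained equations, except for those from dropouts, which will be imputed with the baseline data". Sporadic gaps are multiply imputed; a dropout's missing visits get one fixed value.
- **Statistical Analysis, status of the rule:** the sentence just before it reads "Intention-to-treat procedures will be applied to the data sets obtained". Per-protocol, as-treated and complete-case analyses "will only be performed to assess the robustness of the data analyses". The baseline rule therefore belongs to the main analysis.
- **Statistical Analysis, model:** "A generalized linear mixed model will be used to compare between-group differences in changes of outcome variables at the 12- and 24-week periods".
- **Sample Size Calculation:** "Aiming to achieve a large effect size of 0.8", "using a significance level of 0.05, power level of 90%, and 20% drop-out rate", giving 43 per group and 172 in total.
- **Introduction, fifth objective:** some effects are expected to last, while others "will partially relapse after the intervention cessation".

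The article gives no reason for the baseline rule.

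**The concern.** Setting a dropout to baseline asserts that the patient did not change at all. The Study Design section describes patients who are recovering, and entry is allowed from 4 weeks after discharge. If untreated patients improve, zero change is wrong for dropouts in every arm, and the error enters the between-group difference.

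Arms also differ in burden: 36 exercise sessions with 12 education sessions in the exercise arms, and no treatment for 24 weeks on the waiting list. Equal dropout cannot be taken for granted.

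Two results are at stake. One is the main between-group difference, at a dropout rate the plan itself expects. The other is the fifth objective, because a patient measured at week 13 and lost before week 25 has the missing week-25 value set to baseline, which looks like complete relapse.

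**Working it through.** **Inputs from the article:** effect 0.8 SD, two-sided alpha 0.05, power 90%, dropout 20%, 43 per group, visits at baseline, week 13 and week 25.

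**Assumptions (not in the article):** mean natural recovery r from 0 to 0.8 SD; treated dropout dT and control dropout dC from 10% to 30%; change-score SD of 1; dropouts would have followed their own arm's mean course. Positive change means improvement.

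**1. The plan's own figure.** A two-sample t-test with d = 0.8, alpha 0.05 and power 90% needs 33.8, so 34 per group. 34/(1 − 0.20) = 42.5, so 43 per group and 4 × 43 = 172. The stated size is reproduced.

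**2. Expected difference under the rule.** The treated mean change is (1 − dT)(r + 0.8) and the control mean change is (1 − dC)r. Their difference is

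0.8(1 − dT) + r(dC − dT).

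| dT / dC | r = 0 | r = 0.5 | r = 0.8 |
|---|---|---|---|
| 20% / 20% | 0.64 | 0.64 | 0.64 |
| 30% / 10% | 0.56 | 0.46 | 0.40 |
| 25% / 15% | 0.60 | 0.55 | 0.52 |
| 15% / 25% | 0.68 | 0.73 | 0.76 |
| 10% / 30% | 0.72 | 0.82 | 0.88 |

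**3. Power at the planned 20% in both arms.** An arm with dropout d and mean change m among those who stay has variance (1 − d) + d(1 − d)m². With 43 per arm, SE = √[(vT + vC)/43], and power is about Φ(0.64/SE − 1.96).

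- r = 0: vT = 0.80 + 0.16 × 0.8² = 0.902, vC = 0.80, SE = 0.199, power about 0.90.
- r = 0.5: vT = 0.80 + 0.16 × 1.3² = 1.070, vC = 0.84, SE = 0.211, power about 0.86.
- r = 0.8: vT = 0.80 + 0.16 × 1.6² = 1.210, vC = 0.902, SE = 0.222, power about 0.82.

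Simulation with t-tests (5,000 runs) gave 0.90, 0.85 and 0.82. A completers' comparison under the same non-informative dropout, standing in for a missing-at-random analysis, gave a difference of 0.80 and power of 0.90.

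**4. No true effect.** The expected difference reduces to r(dC − dT), which is zero if dropout is equal or r = 0.

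| Dropout gap | r = 0.5 | r = 0.8 |
|---|---|---|
| 20 points (30% v 10%) | 0.10 SD, type I error about 8% | 0.16 SD, about 12% |
| 10 points (25% v 15%) | 0.05 SD, about 6% | 0.08 SD, about 7% |

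For the first cell: vT = 0.70 + 0.21 × 0.25 = 0.7525, vC = 0.90 + 0.09 × 0.25 = 0.9225, SE = 0.197, 0.10/SE = 0.51, so the two-sided rejection probability is about 0.08.

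**5. Artificial relapse.** If a share f leaves between weeks 13 and 25 and a gain m was in truth fully kept, the mean change from week 13 to week 25 is −f × m.

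- f = 5%, m = 0.5 SD: −0.025 SD
- f = 10%, m = 0.5 SD: −0.05 SD
- f = 10%, m = 0.8 SD: −0.08 SD
- f = 20%, m = 1.3 SD: −0.26 SD

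Patients lost before week 13 hold the baseline value at both visits and add no relapse.

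**The case against.** **Natural recovery is assumed.** The article calls patients recovering but never says how much untreated patients improve. It sets no upper limit on time since discharge, requires persisting impairment, and cites symptoms in 74% to 87% at 2 to 3 months. It gives one overall dropout figure and none by arm. This stands: the null bias and most of the power loss are conditional. The attenuation to 0.64 does not depend on r.

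**Dropouts may lose the benefit.** If so, an all-randomised effect nearer 0.64 could be right, and missing at random could overstate it. This also stands, and is why the fix includes a reference-based analysis. It does not rescue the baseline rule, which removes natural recovery as well as treatment benefit.

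**Complete-case analysis is planned, and the list of sensitivity analyses is open-ended.** A discrepancy may therefore become visible. The main result would still be the baseline-imputed one.

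A reader might also infer four stronger points that the documents do not support:

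- *The variance of change is understated.* Not in general: at 20% dropout and a mean change of 1.3 SD the treated-arm variance is 1.07, above 1, and the t-test holds its 5% level under equal dropout.
- *The arm that loses more sets the direction of bias.* With a real effect this fails: at 15% treated and 25% control dropout with r = 0.5, the estimate is 0.73, still attenuated.
- *The observed week-13 gain is thrown away.* The rule fills missing values only, so that observation stays in the model.
- *Two missing-data assumptions in one analysis are contradictory.* Treating sporadic gaps and dropout differently is not in itself an error.

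**Conclusion.** The point holds in conditional form. The article fixes a single baseline imputation for dropouts in the main analysis. Provided dropouts would have followed their arm's mean course, the planned 20% dropout in both arms reduces 0.80 SD to 0.64 SD. The planned 90% power becomes about 0.82 to 0.86 for recovery of 0.5 to 0.8 SD and is essentially unchanged with no recovery.

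False positives need both unequal dropout and natural recovery. Under the assumed ranges the type I error is about 8 to 12% for a 20-point gap and 6 to 7% for a 10-point gap. The rule therefore cannot be defended as simply conservative, but the article does not show that inflation will occur.

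The distortion at week 25 equals the share lost after week 13 times the gain, and is modest unless late dropout is substantial. It still falls directly on the question of lasting effect versus relapse.

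**What to change.** In the main analysis, handle dropouts under missing at random, in one of two ways that use methods already in the plan:

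- fit the mixed model to all observed visits without filling in dropouts; or
- extend the chained-equation multiple imputation to dropouts, by arm, using baseline and week-13 values.

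Keep baseline imputation as a labelled sensitivity analysis. Beside it, add a reference-based multiple imputation that gives dropouts the waiting-list course, to cover the case where they lose the treatment benefit.

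The cost is a changed sentence or two in Statistical Analysis, made before the data are unblinded, and a little more programming. No more patients are needed: with non-informative dropout, 43 per group keeps 90% power. The downside is that missing at random may overstate the effect if dropouts lose benefit; the reference-based analysis shows by how much.

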### Data Sharing

All individual participant data collected during the trial will be deidentified and will be available to anyone who wishes to access the data immediately following publication.

## Results

The trial was approved by the university ethics committee following the Declaration of Helsinki (REC/19-20/0504) in 2020. The trial has been recruiting patients. The data collection will be completed in 24 months, from January 01, 2021, to December 31, 2022.

## Discussion

As revealed in recent studies, long-term (12 weeks or more) interval exercise can significantly improve ventilatory, central hemodynamic, and peripheral muscle capacities [50]. During the COVID-19 pandemic, home-based tele-coaching techniques, such as a smartphone and step counter, could provide a comfortable and safe environment for rehabilitation that is as effective as that of hospital-based rehabilitation [51-53].

Because of the focus on rehabilitation, using a combination of exercise and Chinese medicine, and exploring the role of the gut microbiome in a mechanistic manner, the proposed study would be the first of its kind for this type of experimental intervention. Given that COVID-19 could persist in human populations, the important findings from this study would provide valuable insights into the mechanisms and processes that are active during rehabilitation.

The proposed multiple components of the rehabilitation program will benefit patients post–COVID-19 who use the various treatment modalities in the process. The findings and implications of this study will have long-lasting positive health benefits for patients with COVID-19 and will help treat related comorbidities. The findings from the study will also provide economic comparative data relating to the development of a cost-effective model for postevent rehabilitation of patients with COVID-19.

## Abbreviations

3-NPH: 3-nitrophenylhydrazine
6MWT: six-minute walk test
BDNF: brain-derived neurotrophic factor
Borg CR10 Scale: Borg Category-Ratio 0-10 Scale
CPET: cardiopulmonary exercise test
CV: coefficient of variation
DSMB: Data and Safety Monitoring Board
ELISA: enzyme-linked immunosorbent assay
FeNO: fractional exhaled nitric oxide
FEV1: forced expiratory volume
FVC: forced vital capacity
GSM: global system for mobile communication
IMT: inspiratory muscle training
KEGG: Kyoto Encyclopedia of Genes and Genomes
PCO_2_: partial pressure of carbon dioxide
QC: quality control
QoL: quality of life
RQ: respiratory quotient
SpO_2_: oxygen saturation as measured by pulse oximetry
SSL: secure sockets layer
UPLC-QTOF-MS: ultra-performance liquid chromatography coupled with quadrupole/time-of-flight mass spectrometry
UPLC-TQ-MS: ultra-performance liquid chromatography triple quadrupole mass spectrometry
VCO_2_: carbon dioxide output
VE: ventilation
VO_2_: O_2_ uptake
